## Abstract

**Background:**

Post–COVID-19 syndrome (PCS; also known as “long COVID”) is a relatively novel disease comprising physical, psychological, and cognitive complaints persisting several weeks to months after acute infection with SARS-CoV-2. Approximately 10% of patients with COVID-19 are affected by long-term symptoms. However, effective treatment strategies are lacking. The ErgoLoCo (Occupational Therapy [Ergotherapie] for Long COVID) study was designed to develop and evaluate a novel occupational therapy (OT) concept of online delivery of therapy for long COVID.

**Objective:**

The primary study objective is to assess the feasibility of the online OT intervention in PCS. Secondary aims include the evaluation of online OT concerning cognitive problems, occupational performance, and social participation.

**Methods:**

This randomized controlled interventional pilot study involves parallel mixed methods process analyses and a realist evaluation approach. A total of 80 clients with PCS aged at least 16 years will be recruited into two interventional groups. The control cohort (watch and wait) comprises 80 clients with long COVID. Treatment is provided through teletherapy (n=40) or delivery of prerecorded videos (n=40) using the same standardized OT concept twice weekly over 12 weeks. Analyses of quantitative questionnaires and qualitative interviews based on the theoretical framework of acceptability will be performed to assess feasibility. Focus group meetings will be used to assess how acceptable and helpful the intervention was to the participating occupational therapists. Standardized tests will be used to assess the initial efficacy of the intervention on neurocognitive performance; limitations in mobility, self-care, and everyday activities; pain; disabilities; quality of life (QoL); social participation; and anxiety and depression in PCS, and the possible effects of online OT on these complaints.

**Results:**

The German Ministry of Education and Research provided funding for this research in March 2022. Data collection took place from October 2022 to August 31, 2023. Data analysis will be completed by the end of April 2024. We anticipate publishing the results in the fall of 2024.

**Conclusions:**

Despite the enormous clinical need, effective and scalable treatment options for OT clients who have PCS remain scarce. The ErgoLoCo study will assess whether online-delivered OT is a feasible treatment approach in PCS. Furthermore, this study will assess the effect of the intervention on cognitive symptoms, QoL, and occupational performance and participation in everyday life. Particular emphasis will be placed on the experiences of clients and occupational therapists with digitally delivered OT. This study will pave the way for novel and effective treatment strategies in PCS.

**Trial Registration:**

German Clinical Trial Registry DRKS00029990; https://drks.de/search/de/trial/DRKS00029990

**International Registered Report Identifier (IRRID):**

PRR1-10.2196/50230

## Introduction

### Background

Post–COVID-19 syndrome (PCS; also known as post–COVID-19 condition or long COVID) is defined as chronic health challenges persisting for more than 4 weeks after an acute SARS-CoV-2 infection. PCS affects a substantial proportion of COVID-19 survivors [1], with an estimated risk of approximately 10% after each infection [2-5]. PCS is a heterogeneous condition that can include symptoms of respiratory impairment, prolonged fatigue, and neurocognitive sequelae [6-8]. Systemic, endothelial, and neuroinflammatory processes, along with reactivation of latent pathogens are suspected contributors to PCS development. However, the immunological and pathological mechanisms of PCS remain unclear and specific treatment options are scarce [9]. Importantly, due to the large number of individuals faced with this condition, PCS considerably impacts communities and health care systems worldwide [10].

Patients with PCS report substantial limitations in their everyday lives [11]. Classic PCS symptoms include problems in concentration and cognitive function, often described as “brain fog,” fatigue, and postexertional malaise. Individuals living with PCS often struggle to participate in everyday contexts such as in work, leisure, self-care, and social interaction [7,12]. Therapy guidelines such as the British National Institute for Health and Care Excellence recommend an integrative, multidisciplinary approach to treating PCS, aiming at symptom management and reduction of functional impairments [11]. Occupational therapy (OT) is central in this multidisciplinary approach [13-15], as it has been shown to improve quality of life (QoL) for individuals with PCS by enabling self-management and coping strategies and accelerating the return to relevant everyday activities in self-care, productivity, and leisure [16].

In most fields of medicine, isolation measures during the COVID-19 pandemic led to further development of online care provision [17-19]. Digital treatment strategies hold great promise for individuals with PCS, who often experience impaired mobility, as these strategies facilitate therapy access and adherence [20].

The ErgoLoCo (Occupational Therapy [Ergotherapie] for Long COVID) study will evaluate the role of digitally delivered OT treatment strategies for clients with PCS. This unblinded, randomized pilot study tests the feasibility and effect of a digitally delivered 12-week online OT program in PCS. The program is delivered either via personal digital visit sessions (teletherapy) or through prerecorded videos (video therapy), focusing on symptom management for cognitive impairment in PCS and improvement of occupational performance in relevant activities of daily life. Our purely digital and scalable approach may help bridge health care gaps and facilitate treatment access for clients with PCS.

### Objectives

This pilot study hypothesizes that an online-administered OT treatment program for individuals affected by PCS is a suitable form of intervention to reduce symptoms and improve occupational performance and QoL. The primary objective is to assess the feasibility of the ErgoLoCo concept by collecting data on participation rates, participant satisfaction, and experience. Secondary aims include analyzing changes in cognitive performance, occupational performance, QoL, and social participation. We here outline the study design and protocol according to the CONSORT (Consolidated Statement of Reporting Trials) guidelines [21].

## Methods

### Study Setting

The ErgoLoCo study centers are located in Lower Saxony, Germany, at the Department for Rheumatology and Immunology of Hannover Medical School and the Department of General Practice of the University Medical Center Goettingen. Data analyses will be conducted at the Ostfalia University of Applied Sciences in Braunschweig. Lower Saxony is Germany’s second-largest federal state with approximately 8 million residents [22]. The number of people affected by PCS in this federal state is unclear. Based on data from a study on cases of illness and death associated with COVID-19 in Lower Saxony, approximately 3,528,782 people had experienced a reported infection with SARS-CoV-2 by the end of 2022 [23].

### Study Design

This pilot study is a 12-week unblinded randomized controlled trial with two intervention groups (group 1: teletherapy/live online; group 2: video on demand) in comparison to a control group (group 3: watch and wait). The study is designed to evaluate feasibility and acceptability, as well as to obtain preliminary evidence on efficacy. The observational period comprises 24 weeks: a baseline assessment (T0) and a 12-week intervention phase with subsequent online questionnaire and testing (T1). At week 24 (T2), study participants will be asked to fill out questionnaires and participate in interviews, and a second round of online testing will be conducted. Given the digital nature of ErgoLoCo, the entire study process, including enrollment, treatment, interviews, and testing, will be performed through online visits.

### Participants

The study will enroll individuals 16 years and older with PCS symptoms persisting at least 4 weeks after confirmed SARS-CoV-2 infection. We will enroll a convenience sample of 120-150 participants.

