### Randomization

Directly after enrollment, urn randomization will be carried out to ensure a balanced distribution of the participants across groups, as shown in Figure 1. Randomization will be performed by an independent study group member not involved in the study design or OT delivery.

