### Intervention Delivery

After randomization, each participant is interviewed by an occupational therapist to assess occupational performance challenges in their everyday occupations, using the German version of the Canadian Occupational Performance Measure (COPM) [27]. The COPM has been validated in various OT intervention studies, which provides metrics on changes in occupational performance, satisfaction and importance, and enhancing transparency in OT outcomes [26,34-37].

The teletherapy/live online group (group 1; n=40) will undergo online OT by a professional occupational therapist via teletherapy twice week using the medical communication and conference software medflex, which ensures data security compliant with the German General Data Protection Guidelines, Datenschutz-Grundverordnung. Video group participants (group 2; n=40) will receive digital OT through prerecorded videos twice weekly. Group 2 participants will receive emails every 2 weeks with links to four online videos illustrating the next intervention module. The participants in this group are asked to watch two videos per week. Intervention groups 1 and 2 will receive both a printed and digital version of a workbook that visualizes and supports all tasks performed throughout the program. The control group (group 3; n=80) is a watch-and-wait group, and these participants will receive the video-on-demand- materials after study completion.

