### Analytical Approach

#### Power and Sample Size

The main focus of this study is to assess the feasibility and acceptability of the intervention. Therefore, efficacy analyses with regard to secondary outcomes will only be exploratory. The pilot study is not sufficiently powered to evaluate the effectiveness of the intervention. However, exploratory analyses will address potential differences in outcomes of cognitive function, QoL, occupational performance, and social participation between the intervention and control groups. No previous reports on OT concepts in PCS or online OT in general were available that could have been used to estimate sample sizes. As current practice standards suggest that formal sample size calculations are unsuitable for feasibility trials, the convenience sample of 120-150 participants was selected pragmatically [43].

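### The arm sizes add up to 160 participants, but the stated enrolment is 120-150, and the allocation ratio is never given in words

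*Protocol article*

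**What the plan says.** The total is given twice. Participants: "We will enroll a convenience sample of 120-150 participants". Power and Sample Size: "the convenience sample of 120-150 participants was selected pragmatically".

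The arm sizes are also given more than once. The Abstract (Methods) says "A total of 80 clients with PCS aged at least 16 years will be recruited into two interventional groups", divides these into 40 for teletherapy and 40 for video, and adds "The control cohort (watch and wait) comprises 80 clients with long COVID". Intervention Delivery repeats the sizes: "The teletherapy/live online group (group 1; n=40) will undergo online OT", 40 again for the video group, and "The control group (group 3; n=80) is a watch-and-wait group". The section on the primary end points puts the two intervention groups together at 80.

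On allocation, Randomization says only that "urn randomization will be carried out to ensure a balanced distribution of the participants across groups", and points to Figure 1, which is not shown in the text available for review.

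**The concern.** The planned total, the arm sizes and the allocation ratio are basic design facts, and a reader should be able to derive each from the others. Here that fails. Each side of the conflict is stated more than once, so it cannot be put down to a single slip.

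Participation rates are among the feasibility data named under Objectives. A reader who wants to know whether recruitment succeeded has no single target: 140 enrolled would lie inside 120-150 but fall 20 short of 160. The Discussion says that later publications will reference this protocol, so the conflict would carry into the results reports.

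**Working it through.** **Inputs**
- Active arms: 40 and 40 (Abstract, Methods; Intervention Delivery). The primary end points section gives 80 for both together.
- Control arm: 80 (Abstract, Methods; Intervention Delivery).
- Total enrolment: 120-150 (Participants; Power and Sample Size).
- The article gives no dropout allowance and no power calculation, so there is no sample size formula to reproduce. The check is a sum.

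**Step 1: sum of the arms.** 40 + 40 + 80 = 160.

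**Step 2: comparison with the stated range.**
- Against the upper end: 160 − 150 = 10, and 10/150 = 6.7%.
- Against the lower end: 160 − 120 = 40, and 40/120 = 33%.

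**Step 3: what the stated range would give.** The sizes 40, 40 and 80 stand in the ratio 1:1:2, so each active arm is N/4 and control is N/2.

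| N | Teletherapy | Video | Control |
|---|---|---|---|
| 120 | 30 | 30 | 60 |
| 150 | 37.5 | 37.5 | 75 |
| 160 | 40 | 40 | 80 |

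Only N = 160 gives the stated arms. If both active arms were held at 40, control would have 120 − 80 = 40 to 150 − 80 = 70 participants, still below 80.

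**Step 4: possible reconciliations.**
- *Attrition.* A fall from 160 to 150 is a loss of 10/160 = 6.25%, and to 120 a loss of 40/160 = 25%. The article, however, presents 120-150 as the number enrolled, not the number completing.
- *Enrolled versus randomised.* Randomization takes place directly after enrolment, and Table 1 puts it at the enrolment time point, so these should be the same people.
- *A control group outside the trial.* Study Design makes group 3 the comparator within the randomised trial, so it counts toward the total.
- *Chance variation of the urn.* An urn lets arm sizes vary around their targets, but the three arms must still add up to the number randomised. It cannot turn 150 into 160.

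None of these closes the gap.

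**The case against.** The best case on the other side is that little depends on the figure. Power and Sample Size says that no formal calculation was made, that the number was chosen pragmatically and that the efficacy analyses are exploratory. No power claim or stated decision rule changes between 120 and 160. This stands, and it limits the consequence, but it does not remove the arithmetic conflict.

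A reader might also infer something stronger: that balance across groups means three equal groups, that the urn therefore contradicts 1:1:2, and that the article describes two different designs. It is tempting because 120-150 divides into thirds of 40 to 50. The text does not support it:
- The Randomization section does not mention equal sizes or thirds. Balance could mean comparable participant characteristics, or 80 treated against 80 control.
- An urn can be weighted. In a simulation of 1000 runs with two of four urn slots given to control, the average was about 40/40/80 at N = 160 (SD about 4 to 5 per arm).
- Figure 1 is not shown and may give the ratio.

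Equal allocation is therefore an inference. What remains is that the section leaves open the urn's target ratio and what it balances.

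**Conclusion.** The concern holds as a conflict between two total sample sizes. The arms require 160 and the stated enrolment is 120-150, a difference of 10 to 40 participants (7% to 33%) that nothing in the text explains. In addition, the ratio has to be inferred from arm sizes that do not fit the stated total.

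This rests on reading 120-150 as the whole trial population, including controls, which is how Participants and Power and Sample Size present it. The documents do not show which figure is the intended one.

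Two further inferences should be avoided. The article does not establish a contradiction between the urn and 1:1:2. Nor does the discrepancy weaken a primary conclusion through loss of power, because the pilot claims no power. It is a required correction of the text with limited consequence for the analysis.

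**What to change.** State one planned total, one set of arm sizes and one explicit allocation ratio, taken from the randomisation specification actually used. Apply them in the Abstract (Methods), Participants, Intervention Delivery, the primary end points section and Power and Sample Size. All the affected figures must change together: if the arms differ from 40/40/80, the 40s and the combined 80 for the intervention groups need correcting as well as the control number. In Randomization, state the urn's target ratio and what it is meant to balance.

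The Abstract (Results) reports data collection as finished on August 31, 2023, although the main Results section still describes it as scheduled. If it is finished, the correction should report what was specified and used; an allocation should not be chosen now. The cost is a few lines of text, with no extra participants and no change to the analysis.

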### Eligibility Criteria

Inclusion criteria are as follows: (1) 16 years or older, (2) affected by persisting health problems beyond 4 weeks after SARS-CoV-2 infection (confirmed either by polymerase chain reaction or rapid antigen testing), (3) personal reporting of subjective cognitive symptoms such as brain fog and fatigue ≥5/10 on a Likert scale, (4) having access to an appropriate technical device to participate in the intervention (eg, PC, tablet, or smartphone with internet access), and (5) provision of written informed consent to participate in the study (in clients <18 years of age, additional written consent is to be provided by legal guardians). Individuals not meeting the above-mentioned inclusion criteria and those lacking the willingness or ability to complete the program consisting of either teletherapy or video sessions will be excluded from the study.

### Recruitment

Potential participants will be recruited via the homepage of participating hospitals and research departments and a prior observational study on PCS (DEFEAT Corona study) [24,25]. Moreover, local private practices and clinics throughout Northern Germany and beyond will be asked to share information on the study with affected clients in their care. Clients interested in participating in the study are asked to register on the DEFEAT study webpage [25].

### Participant Screening

Study eligibility will be evaluated by online questionnaires on self-perceived PCS-related cognitive impairment (eg, brain fog and fatigue scores ≥5/10 or higher on a Likert scale). Eligible participants will receive comprehensive study information as well as an invitation to book an online appointment by email. Upon the first digital visit, study staff will provide further information, discuss possible questions, and recheck eligibility criteria. After obtaining written informed consent by digital signature on an online study inclusion form (including signature of a legal guardian for participants below the age of 18 years), data on age, gender, and health status are collected. Furthermore, information on social participation and subjective well-being are obtained. Participants are also tested for cognitive functions and impairments in daily life (Table 1).

**Table 1 table1:** Schedule for enrollment and assessment.

Stage and outcome		Instrument	Time point
Eligibility screen		Online questionnaire	Enrollment
Informed consent		Digital visit	Enrollment
Randomization		Digital visit	Enrollment
**Mixed methods study on acceptability and feasibility (primary outcome)**			
	Acceptance and feasibility of the online program	Semistructured interviews with 12 participants of each treatment group	Week 6 and week 12
	Acceptance and feasibility of the online program	Questionnaire assessing 35 Likert-scaled items developed based on the theoretical framework of acceptability in all participants [26]	Week 24
	Acceptance and feasibility of the online program	Focus group meeting notes on acceptance and feasibility of the online program by occupational therapists providing live-online sessions	Week 12
**Neurocognitive and occupational impairments (secondary outcomes)**			
	Self-perception of occupational performance in everyday life	Canadian Occupational Performance Measure [27]	Enrollment and week 12
	Memory and cognitive impairment	Wilde-Intelligence test-2, modules MF^a^ and ER^b^ [28]	Enrollment, week 12, and week 24
	Impairment in daily life activities, family and social life, stress, and sexual activity	Index for the Assessment of Health Impairments [29]	Enrollment, week 12, and week 24
	Physical, mental, and social effects of neurological conditions	Quality of Life in Neurological Disorders [30]	Enrollment, week 12, and week 24
	Deficits in concentration, attention [31], and mental speed	D2 test of attention-revised [31]	Enrollment, week 12, and week 24
	Mobility, self-care, usual activities, pain, disabilities, anxiety, and depression	EQ-5D-5L [32]	Enrollment, week 12, and week 24

### Randomization

Directly after enrollment, urn randomization will be carried out to ensure a balanced distribution of the participants across groups, as shown in Figure 1. Randomization will be performed by an independent study group member not involved in the study design or OT delivery.

**Figure 1 figure1:**
[figure not shown]
Process flowchart of the ErgoLoCo study. OT: occupational therapy.

### Intervention

The OT concept was designed using the Medical Research Council Framework, ensuring evidence-based and theory-based OT-specific approaches [33]. These approaches will be identified using a literature review, including the English, Dutch, and German literature. Furthermore, we will include stakeholder experiences in treating clients with PCS in inpatient and outpatient settings in Germany, Austria, and Switzerland. The OT concept will include 24 30-minute standardized therapy sessions. Each session will be delivered twice a week over 12 weeks. Therapy sessions consist of OT-specific instructions for managing PCS symptoms, which will be tailored to individual aims defined for each OT recipient upon entering and throughout the program. Participants will receive an accompanying workbook with materials to support therapy transfer into everyday life.

### Intervention Delivery

After randomization, each participant is interviewed by an occupational therapist to assess occupational performance challenges in their everyday occupations, using the German version of the Canadian Occupational Performance Measure (COPM) [27]. The COPM has been validated in various OT intervention studies, which provides metrics on changes in occupational performance, satisfaction and importance, and enhancing transparency in OT outcomes [26,34-37].

The teletherapy/live online group (group 1; n=40) will undergo online OT by a professional occupational therapist via teletherapy twice week using the medical communication and conference software medflex, which ensures data security compliant with the German General Data Protection Guidelines, Datenschutz-Grundverordnung. Video group participants (group 2; n=40) will receive digital OT through prerecorded videos twice weekly. Group 2 participants will receive emails every 2 weeks with links to four online videos illustrating the next intervention module. The participants in this group are asked to watch two videos per week. Intervention groups 1 and 2 will receive both a printed and digital version of a workbook that visualizes and supports all tasks performed throughout the program. The control group (group 3; n=80) is a watch-and-wait group, and these participants will receive the video-on-demand- materials after study completion.

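### The only baseline COPM is taken after randomisation in an unblinded trial, so knowledge of the arm can shift the reference point for this exploratory outcome

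*Protocol article*

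**What the plan says.** Five places in the protocol article bear on the point.

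- **Intervention Delivery:** "After randomization, each participant is interviewed by an occupational therapist to assess occupational performance challenges in their everyday occupations". The text goes on to name the German version of the COPM as the tool.
- **Table 1, secondary outcomes:** the COPM row covers "Self-perception of occupational performance in everyday life" and gives the time points as "Enrollment and week 12". The other five instruments in that block are also measured at week 24.
- **Study Design:** "This pilot study is a 12-week unblinded randomized controlled trial with two intervention groups". The third group is a watch-and-wait control.
- **Randomization:** "Directly after enrollment, urn randomization will be carried out". An independent study group member does this.
- **Participant Screening:** at the first digital visit, after consent, "Participants are also tested for cognitive functions and impairments in daily life", with a pointer to Table 1. The COPM is not named there.

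The Power and Sample Size section foresees exploratory comparisons of intervention and control groups, with occupational performance among the outcomes. The Statistical Analysis Plan section analyses questionnaire scores as change over time.

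**The concern.** A baseline serves as a neutral reference only if allocation cannot have influenced it. The COPM is open to such influence because the participant's own problems are elicited in an interview and then self-rated. A participant who has just learned that they will wait, or that they are about to start therapy, may name other problems or rate the same ones differently. An interviewer who knows the arm may steer the conversation without meaning to.

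With one baseline and one follow-up, no second pre-treatment COPM value exists against which a shift could be checked. Someone who leaves after learning the allocation but before the interview would also have no baseline, which complicates an intention-to-treat analysis of change. Whether this would happen is not known.

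At stake is the between-arm reading of COPM change. The Discussion says that the intervention was developed to improve occupational performance, so this signal may be carried into later work.

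**Working it through.** **1. Order of events.** There is no stated figure to reproduce: the article has no formal sample-size calculation, SD or effect size. The check is a comparison of sections.

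- Intervention Delivery is the only explicit statement of order, and it puts the COPM after randomisation.
- Table 1 labels the first COPM as enrolment, and Randomization puts allocation directly after enrolment. Read literally, the COPM would come first. But Table 1 also lists randomisation itself under enrolment, so the label does not settle the order.
- The testing described in Participant Screening could include the COPM through its pointer to Table 1. Its wording on impairments in daily life lies closer to the row for the Index for the Assessment of Health Impairments than to the COPM row.
- No section says that the participant or the interviewer is unaware of the arm until the COPM is complete.

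As written, then, the sole COPM baseline follows allocation without protection.

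**2. How a shift carries through.** Let *d* be the between-arm difference at baseline caused by knowledge of the arm, in SD units, and let there be no treatment effect.

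- Difference in mean change: biased by *d* in absolute size, with the opposite sign to the baseline shift.
- SD of the change score: √(2(1 − r)), where r is the correlation between baseline and week 12.
- Standard error: SE = √(2(1 − r)) × √(1/n₁ + 1/n₀).
- False-positive rate of a two-sided 5% test: 1 − Φ(1.96 − d/SE) + Φ(−1.96 − d/SE).

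**3. Illustration.** From Intervention Delivery: one intervention group of 40 against 80 controls, so √(1/40 + 1/80) = 0.1936. Assumed, not in the document: d = 0.2 SD, r = 0.3 to 0.7, no multiplicity correction.

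| r | SD of change | SE | d/SE | False-positive rate |
|---|---|---|---|---|
| 0.3 | 1.183 | 0.229 | 0.87 | 14.1% |
| 0.5 | 1.000 | 0.194 | 1.03 | 17.8% |
| 0.7 | 0.775 | 0.150 | 1.33 | 26.6% |

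**4. Sensitivity.**

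- *Size of shift (40 vs 80, same range of r):* 7.2% to 10.2% at d = 0.1, and 25.8% to 51.6% at d = 0.3.
- *Group sizes:* the named groups sum to 40 + 40 + 80 = 160, whereas Participants gives 120 to 150. With 40 vs 40 (three equal groups of 120 in total), d = 0.2 gives 11.8% to 21.1%. With 50 vs 50 (150 in total) it gives 13.5% to 25.2%.
- *Baseline adjustment:* a model adjusted for the shifted baseline has bias r × d and residual SD √(1 − r²). For 40 vs 80 and d = 0.2 the rate is 6.2% to 17.3%. Adjustment reduces the bias but does not remove it. The article does not plan such a model.
- *Baseline taken before allocation is known:* d = 0, and this component disappears.

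**The case against.** The strongest reply is that this is a possible risk to one exploratory outcome in a feasibility pilot. Much of that stands.

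- **Status.** The COPM is one of six secondary instruments, efficacy analyses are declared exploratory, and the pilot is stated not to be powered for effectiveness. Exploratory status excuses low power but gives no reason to accept a bias that reordering would avoid.
- **Disclosure.** Unblinded does not prove that the arm was known at the interview. That is correct, but nothing in the article prevents it.
- **Interviewer.** A reader might infer that the interviewer is the person's treating therapist. The article does not say so, and the route could apply only to group 1, because group 2 receives prerecorded videos and group 3 waits. The participant's own knowledge of the arm is a route in all groups.
- **Table 1.** A reader might infer that Table 1 contradicts Intervention Delivery. It does not clearly do so, since it places randomisation under the same label. The flowchart cited for randomisation is not available in the text reviewed.
- **Test.** The plan mentions corrections for multiple testing and specifies no between-arm COPM test at 5%, so the rates above are illustrative and do not describe a planned test.
- **Goal-setting.** Therapy is tailored to individual aims set on entry, and the interview may serve that purpose. This does not require it to follow allocation.
- **Follow-up.** The week-12 COPM is self-rated with the arm known, whatever is done at baseline. Reordering removes only the baseline component.

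**Conclusion.** The point holds as a limited but avoidable weakness. As written, the only COPM baseline follows randomisation in an unblinded trial with no stated protection, and any shift it causes enters a between-arm difference in change in full. The order of events rests on the text. The 14% to 27% range rests on an assumed 0.2 SD shift, an assumed correlation of 0.3 to 0.7, and an uncorrected 5% test of 40 versus 80.

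Two stronger conclusions are tempting and unsupported. One is that the COPM results are biased by a known amount or in a known direction: the document supports only the possibility. The other is that the trial's main conclusion is compromised: the primary objective is feasibility, which does not depend on the COPM baseline. Nor would correcting the order make the COPM comparison free of bias, because the follow-up rating remains unblinded.

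**What to change.** Amend Intervention Delivery so that the T0 COPM is completed before randomisation, or at least before allocation is disclosed to the participant and the interviewer. Bring Participant Screening, Table 1 and Randomization into line, so that the sequence of consent, T0 measures, allocation and disclosure reads the same everywhere.

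The interview is already planned for every participant, so the cost is scheduling: a short delay before allocation, and a few interviews with people who drop out before randomisation.

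The Abstract reports data collection in the past tense, as ended on August 31, 2023, while the Results section describes the same period as scheduled. If collection is finished, reordering is no longer possible. The report should then state the order actually used and whether the arm was known at the interview, show baseline COPM scores and missing baselines by arm, and interpret between-arm COPM change with that limitation. This costs a few lines and one table.
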